### 2.6. Study Protocol

Eligible patients will be referred to the Department of Dental Anesthesiology, Showa University, Koto Toyosu Hospital to provide their written informed consent for the present study after an approximately 30 min detailed explanation of the purpose, schedule, risks, merits/demerits, and protocols of the present study by one of the investigators ([name]). This explanation will be associated with a test of the tongue capsule for each candidate. If the tongue capsule does not fit the subject’s tongue or causes excessive irritation/discomfort/soreness, etc., the participant will be excluded from the study. All the candidates will be scheduled for an evaluation of OSA using OCST, as described before. Subjects who are diagnosed with OSA with 10 ≤ REI < 30/h will be scheduled for the RCT, while those with REI < 10/h and 30/h ≤ REI will be excluded from the study at this stage.

Prior to the induction of intravenous sedation on the study day, electrodes for OCST (LS-300, Fukuda Denshi Co., Ltd., Tokyo, Japan) will be attached to a patient sitting on a reclining dental chair to allow for the monitoring of nasal pressure via a nasal cannula to assess nasal airflow, chest wall movements for assessing respiratory efforts, and arterial oxygen saturation (SpO_2_) using pulse oximetry (Figure 4). A routine vital-sign monitor including electrocardiogram, noninvasive blood pressure and an electroencephalogram (Root + SedLine, Masimo Corp., CA, USA) will be attached. Thereafter, one of the investigators ([name]) and the subject will simulate the study with the TPR in place while awake so that it can be smoothly performed under intravenous sedation.

The predetermined random allocation order will be strictly applied to all consecutive consenting patients during the study period. The anesthesiologist ([name]) will be informed of the allocation of the participant immediately before the initiation of intravenous sedation to reduce potential bias. The anesthesiologist will provide conscious intravenous sedation by a bolus intravenous injection of midazolam (1 to 3 mg) and propofol (5 to 10 mg), followed by continuous infusions of propofol (1 to 3 mg kg^−1^ h^−1^) using the target-controlled infusion system [19,20]. After an acclimatization period for TPR (30 s), a baseline evaluation (i.e., no control of tongue position with TPR in place) will be performed (1 min) (Figure 4). Thereafter, each patient will undergo both interventions A (MAX50 for 1 min and MAX 100 for 1 min) and B (1 min) in a randomized order with a washout period (30 s) between the interventions. An ex-post evaluation (1 min) will also be scheduled after removal of the TPR, when both study sequences are complete. After the core part of the present study (i.e., baseline evaluation, interventions, and ex-post evaluation) which will take an average of 6 min, supplemental oxygen at a flow rate of 3 L/min will be provided for the scheduled dental operation.

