## 2. Materials and Methods

### 2.1. Study Design

This is a randomized, controlled, non-blinded, crossover, and two-armed (i.e., sequence AB/BA) clinical trial that will follow the CONSORT 2010 statement, providing an extension to randomized crossover trials to better report the results [9]. An overview of the study is presented in Figure 2, following the recommended template for the schedule of enrollment, interventions, and assessments described by Standard Protocol Items: Recommendation for Interventional Trials (SPIRIT) [10]. Recruitment will last from the day the data are released by the Japan Registry of Clinical Trials (jRCTs) (032220040) (25 April 2022), and the duration of the study itself will start from the day the data are released by jRCTs until 31 March 2026.

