### 2.7. Study Outcome

#### 2.7.1. Primary Outcome

Since this study will be performed under intravenous sedation, and not during sleep, definitions of apnea and hypopnea as alternatives to AHI and REI that occur during sleep need to be prepared for scoring abnormal breathing. In other words, definitions for an intravenous sedation study as an alternative to AHI and REI and other variables for studies during sleep will more reasonably reflect the effects of the intervention on upper airway patency during intravenous sedation, as described in our previous report [20]. Abnormal breathing under intravenous sedation is to be predetermined by OCST based on five expected features of abnormal breathing: (1) obstructive or central, (2) apnea or hypopnea, (3) with or without desaturation, (4) with or without irregular breathing, and (5) bradypnea or tachypnea. Upper airway obstruction is determined by the presence of respiratory effort for an apnea, and the presence of inspiratory flow limitation is evidenced by a flattened nasal pressure signal for a hypopnea. Apnea, expressed as “A”, under intravenous sedation is defined by complete cessation of the nasal pressure changes for more than 10 s, whereas hypopnea, expressed as “H”, under intravenous sedation, is defined as being one of three types: H70, H50 and H30. H70 is defined as a more than 70% reduction in the nasal pressure amplitude for more than 10 s. H50 is defined as a more than 50% reduction in the nasal pressure amplitude for more than 10 s. H30 is defined as a more than 30% reduction in the nasal pressure amplitude for more than 10 s. Desaturation, expressed as “D”, is defined as a more than 2% reduction in SpO_2_ for more than 10 s. Irregular breathing, expressed as “I”, is determined when the nasal pressure signal frequency (respiratory rate) and amplitude fluctuate more than twofold after apnea or hypopnea. Irregular breathing is considered to be elicited by laryngeal stimulation with water inside the oral cavity and subsequent cough reflexes. The abnormal breathing index (ABI) is calculated as the number of these abnormal breathing instances per hour of the study period. The abnormal respiratory time (ART) is the duration of one abnormal breathing and is calculated as a mean and a percentage during study period. Similarly, the ABI of apnea (ABI-A) will be used as the primary outcome for a statistical analysis of the study hypotheses.

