### 2.8. Statistical Analysis

The baseline measures will be compared with the measures obtained under interventions A and B. The normality of data will be tested by the Shapiro–Wilk test. Repeated-measures ANOVA with the Bonferroni correction for multiple testing, followed by Tukey’s honestly significant difference tests will be used as the parametric test for normally distributed data. If the data do not follow a normal distribution, a non-parametric test, the Kruskal–Wallis test with the Bonferroni correction for multiple testing followed by Dunn–Bonferroni tests, will be used. The data will be presented as either the mean ± standard deviation or median (interquartile range) for normal and non-normal distributions. All statistical analyses will be performed using SPSS software (version 25, IBM Japan, Tokyo, Japan). All *p* values are two-tailed and a *p* value of <0.05 is considered to indicate statistical significance.

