The present study and other similar studies have significant limitations, which will certainly provide challenges to overcome and opportunities to polish the study design. The participants will be patients who are originally scheduled to undergo a dental operation under intravenous sedation as soon as the study ends, indicating that the number of expected OSA samples will be limited. Moreover, we will use OCST for the evaluation of outcomes, since it is not feasible for us to perform polysomnography under the perioperative circumstances in the dental operation room. Patients whose baseline REI is <10/h will not be recruited, because our previous study demonstrated that these individuals will easily achieve the variety criteria for treatment success (e.g., more than 50% reduction in baseline AHI and/or follow-up AHI < 5/h with more than 50% reduction in baseline AHI) in oral appliance therapy [13]. Additionally, subjects with 30/h ≤ baseline REI (i.e., severe OSA) will not be included to minimize the confounding effects on primary and secondary outcomes. Conversely, an RCT under intravenous sedation is a meritorious study design to obtain outcomes with a higher evidence level within a limited time, as with our previous study [20]. Although the administration of propofol for intravenous sedation was reported to suppress REM sleep, and a greater suppression of upper airway muscle activity than in natural sleep can also occur, the sedation level can be carefully targeted to a certain level of sleep (e.g., stage II non-REM sleep) throughout the study as long as this is under the control of a skilled anesthesiologist with the target-controlled infusion system [19,20,22,23]. Additionally, the identification of the site of occlusion during intravenous sedation/sleep and site of action of TPR is also an important concern in future studies in order to increase the success rate of TPR treatment. In the human pharynx, three segments are present: the velopharynx (from the level of the hard palate to the free margin of the soft palate), oropharynx (from the free margin of the soft palate to the tip of the epiglottis), and hypopharynx (from the tip of the epiglottis to the vocal cords) [24,25]. The most common site of occlusion is the velopharynx, although upper airway narrowing also occurs in the oropharynx in OSA [24,26]. Notably, Kuna and Remmers stated there is no simple occlusion at the oropharynx [24]. The authors support these previous reports with regard to the site of occlusion because such conclusions were drawn by direct observation of the upper airway narrowing either at the passive or asleep pharynx using endoscopes, whereas a recent report demonstrated that the tongue-based obstruction of upper airway was successfully identified using ultrasound and magnetic resonance imaging [24,26,27]. Finally, a similar RCT protocol to the present study needs be designed for female OSA patients in future.

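### The trial is declared non-blinded without exception, and no masking is described for scoring the recorded sedation traces, although they could be read masked to condition and sequence

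*Protocol article*

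**What the plan says.** Section 2.1 of the Protocol article states: "This is a randomized, controlled, non-blinded, crossover, and two-armed (i.e., sequence AB/BA) clinical trial". The Abstract repeats the label. Neither place makes an exception for outcome assessment.

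Section 2.6 fixes when the order is revealed: the anesthesiologist "will be informed of the allocation of the participant immediately before the initiation of intravenous sedation to reduce potential bias". The same person then gives the sedation, with doses stated as ranges. After 30 s of acclimatization comes the comparator window: "a baseline evaluation (i.e., no control of tongue position with TPR in place) will be performed (1 min"). Interventions A (two 1-min steps) and B (1 min) follow in the randomized order, 30 s apart. Section 2.8 uses the baseline as the reference for both: "The baseline measures will be compared with the measures obtained under interventions A and B".

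Section 2.7.1 defines the outcomes on recorded signals. An apnea is a complete stop in nasal pressure change lasting more than 10 s. Hypopneas are graded by reductions of more than 30%, 50% or 70% in amplitude, and for obstruction "the presence of inspiratory flow limitation is evidenced by a flattened nasal pressure signal for a hypopnea". The section does not say who scores the sedation traces or what that person knows. Registered technologists are named only for the eligibility sleep test (Section 2.3.1).

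**The concern.** Two kinds of masking need to be kept apart. The person holding the device knows the tongue position and cannot be masked. The person reading the trace afterwards does not need to know it, because every outcome is taken from a stored recording. A blanket non-blinded label gives up the second kind of masking along with the first, and no passage takes it back.

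This matters because scoring involves judgement (whether a signal is flattened, whether flow has truly ceased, whether an interval exceeds 10 s) and because the expected ranking is written down beforehand. The Introduction states it as the hypothesis, and the Conclusions word it as a result. A reader of the traces who knows the condition may, without intending to, resolve borderline events in that direction.

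The timing of disclosure is a smaller matter. Revealing the order just before sedation protects enrolment. It does not protect what comes after it, and nothing described before the end of the baseline minute depends on the order.

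**Working it through.** **Inputs**
- Window lengths (Section 2.6): baseline 1 min; B 1 min; A two steps of 1 min, 2 min in all.
- Index (Section 2.7.1): number of events per hour. Assumption: it is computed separately for each condition window, since otherwise conditions could not be compared.
- Sample size (Section 2.5): 9 per group, 18 in total, 26 after 30% drop-out.
- Planning values (Section 2.5): AHI 21.8 ± 8.6/h falling to 9.3 ± 5.8/h.

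**The plan's own figures.** The planning difference is 21.8 − 9.3 = 12.5/h. A two-sample t test with SD 8.6, two-sided alpha 0.05 and power 0.80 gives 9 per group (power 0.825), so 18. Then 18/(1 − 0.30) = 25.7, so 26. These figures reproduce. The point does not depend on them; they only supply the denominators 18 and 26 below.

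**Step size in one participant.** One event in a window of w minutes equals 60/w per hour.
- w = 1: 60/1 = 60/h.
- w = 2 (all of A as one window): 60/2 = 30/h.

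A pause judged slightly longer rather than slightly shorter than 10 s therefore moves that participant's 1-min value by 60/h.

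**What this does to a condition mean.** If m of N participants each have one event scored differently in the same direction, the mean moves by m × step/N.

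| m | Step | N | Shift in mean |
|---|---|---|---|
| 1 | 60/h | 18 | 60/18 = 3.3/h |
| 1 | 60/h | 26 | 60/26 = 2.3/h |
| 4 | 60/h | 18 | 240/18 = 13.3/h |
| 4 | 60/h | 26 | 240/26 = 9.2/h |
| 4 | 30/h | 18 | 120/18 = 6.7/h |

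The choice of m = 4, all in one direction, is arbitrary. The table shows how coarse the scale is, not how much bias to expect.

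**Does an uncut trace hide the order?** No. A occupies 2 min and B 1 min with 30 s between them, so the timing alone shows which came first. Withholding the allocation list from the scorer would not be enough; the trace has to be cut.

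**What does disclosure before baseline add?** Up to the end of the baseline minute the described steps are sedation, acclimatization and a minute with the device in place and no tongue control. They are the same for AB and BA, so none uses the sequence.

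**The case against.** The case on the other side is substantial on sedation and partly right on scoring.

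*Sedation and baseline.* A reader might infer that knowing the order lets the anesthesiologist shift the baseline, or tilt A against B. The documents do not support so strong a reading. Baseline comes first and is the same condition in both sequences, so an operator who wanted a poor baseline would not need the allocation. Both interventions follow one induction, and their order is randomized about one to one. Tilting A against B would take changes in sedation between the periods, when the operator must know the position anyway. Target-controlled infusion and EEG monitoring (Section 2.6), and the stated intention that "the sedation level can be carefully targeted to a certain level of sleep (e.g., stage II non-REM sleep) throughout the study" (Section 3), narrow the discretion further. What stands is only the limited risk that induction is titrated differently for AB and BA.

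*The stated reason for the timing.* Revealing the order after consent and eligibility testing is sound allocation concealment, and the sentence does not claim to mask the operator.

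*Silence on scoring.* The article condenses a fuller protocol, and the label does not say who is unmasked. It therefore cannot be said that the scorers are known to be unmasked. The label itself is nevertheless an explicit, unqualified design statement. If the full protocol does mask the scoring, the label misdescribes the trial and should be corrected.

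*The primary outcome is the firmer one.* Complete cessation for more than 10 s is a tighter rule than flattening or percentage reduction, so the hypopnea outcomes are more exposed than ABI-A. Both still have borderline cases.

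*Magnitude.* One might set 13.3/h against 12.5/h and conclude that scoring bias would exceed the planned effect. That comparison does not hold. Four same-direction changes is an arbitrary number, other reasonable denominators give 9.2 or 6.7/h, and 12.5/h is an AHI difference from a study of another device, not a planned ABI-A difference under sedation.

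**Conclusion.** The point holds for outcome scoring: the trial is called non-blinded throughout, no masking of trace scoring is described, and masked scoring is feasible. One borderline apnea changes ABI-A by 60/h in a participant for a 1-min window, or 30/h if A is scored as one 2-min window. Scoring decisions can therefore matter, but the documents give no basis for predicting how large or in which direction any bias would be. This rests on two assumptions: that the index is computed per condition window, and that no masked scoring is laid down in the full protocol. The timing of disclosure is a minor, secondary matter and no evidence that the baseline or the A-versus-B comparison is compromised.

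**What to change.** 1. Cut each recording into coded 1-min segments (baseline, each step of A, B, and the final minute after device removal) with clock time removed. Equal lengths are needed because 2 min of A against 1 min of B reveals the order.
2. Supply every segment with a common reference amplitude, since the 30%, 50% and 70% criteria cannot be applied to an isolated minute without one.
3. Have whoever already scores the sedation traces read the segments in random order, masked to condition and sequence, and state that role in Section 2.7.1.
4. Describe the trial in the Abstract and Section 2.1 as open-label with masked outcome scoring.
5. As a secondary step, open the allocation after the baseline minute, just before the first device position, and reword the stated reason in Section 2.6 accordingly. This removes only the risk that induction differs by sequence; it does not mask the operator during the interventions.

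The cost is file coding before scoring and an allocation opened later by the induction time (not given) plus 30 s and 1 min. Sedation, device steps and sample size are unchanged. Where recordings have been kept, participants already studied can be scored in the same way.

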### 2.7. Study Outcome

#### 2.7.1. Primary Outcome

Since this study will be performed under intravenous sedation, and not during sleep, definitions of apnea and hypopnea as alternatives to AHI and REI that occur during sleep need to be prepared for scoring abnormal breathing. In other words, definitions for an intravenous sedation study as an alternative to AHI and REI and other variables for studies during sleep will more reasonably reflect the effects of the intervention on upper airway patency during intravenous sedation, as described in our previous report [20]. Abnormal breathing under intravenous sedation is to be predetermined by OCST based on five expected features of abnormal breathing: (1) obstructive or central, (2) apnea or hypopnea, (3) with or without desaturation, (4) with or without irregular breathing, and (5) bradypnea or tachypnea. Upper airway obstruction is determined by the presence of respiratory effort for an apnea, and the presence of inspiratory flow limitation is evidenced by a flattened nasal pressure signal for a hypopnea. Apnea, expressed as “A”, under intravenous sedation is defined by complete cessation of the nasal pressure changes for more than 10 s, whereas hypopnea, expressed as “H”, under intravenous sedation, is defined as being one of three types: H70, H50 and H30. H70 is defined as a more than 70% reduction in the nasal pressure amplitude for more than 10 s. H50 is defined as a more than 50% reduction in the nasal pressure amplitude for more than 10 s. H30 is defined as a more than 30% reduction in the nasal pressure amplitude for more than 10 s. Desaturation, expressed as “D”, is defined as a more than 2% reduction in SpO_2_ for more than 10 s. Irregular breathing, expressed as “I”, is determined when the nasal pressure signal frequency (respiratory rate) and amplitude fluctuate more than twofold after apnea or hypopnea. Irregular breathing is considered to be elicited by laryngeal stimulation with water inside the oral cavity and subsequent cough reflexes. The abnormal breathing index (ABI) is calculated as the number of these abnormal breathing instances per hour of the study period. The abnormal respiratory time (ART) is the duration of one abnormal breathing and is calculated as a mean and a percentage during study period. Similarly, the ABI of apnea (ABI-A) will be used as the primary outcome for a statistical analysis of the study hypotheses.

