### 2.5. Sample Size and Allocation Concealment Mechanism

In a previous study that evaluated the effect of tongue protrusion using a tongue-stabilizing device on the severity of OSA, Apnea Hypopnea Index (AHI) improved from 21.8 ± 8.6/h to 9.3 ± 5.8/h [18]. This indicates that, if intervention B is applied to a participant, there should be no change in AHI. Therefore, our null hypothesis is that the mean AHI was not different between intervention A (μ1) and intervention B (μ2) (i.e., μ1 = μ2), whereas the alternative hypothesis is that the mean AHI of intervention B is greater than that of intervention A (i.e., μ1 < μ2). The effect size (Δ0) and the power (i.e., 1-β) should be calculated with the following formula: Δ0 = (μ1 − μ2)/σ, 1 − β = Pr{t0 < −t(φ, 2α)}, φ = n1 + n2 − 2, where σ is the population standard deviation, β is the Type II error, φ is the degree of freedom, α is the Type I error set at 0.05, n1 is the number of subjects with intervention A, and n2 is the number of subjects with intervention B. Statistically, n1 and n2 are assumed to be equal (i.e., n1 = n2) to each other and 1-β is set at 0.80. Consequently, each intervention group needs 9 participants (i.e., 18 participants for both groups). If the drop-out rate is set rather high, at 30%, the study needs 25.7 samples; thus, a total of 26 participants will be required to test the hypothesis.

These 26 participants are to be randomized by creating a computer-generated randomization list using the permuted block method (Mujinwari, https://mujinwari.biz, Iruka-system, Tokyo, Japan: accessed on 28 May 2023) with random block sizes of two or four, stratified by body mass index (<25 kg/m^2^ or 25 kg/m^2^≤). Consequently, participants will be assigned random numbers based on consecutive enrollment into either sequence AB or sequence BA, which provides an approximately one-to-one ratio for the number of subjects in the two sequences.

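### The 80% power claim is computed from sleep AHI figures and does not carry over to ABI-A, an apnea count from a 1-minute window

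*Protocol article*

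**What the plan says.** Section 2.5 takes its planning values from an earlier study of a tongue-stabilizing device, in which "Apnea Hypopnea Index (AHI) improved from 21.8 ± 8.6/h to 9.3 ± 5.8/h". It assumes that "if intervention B is applied to a participant, there should be no change in AHI", so B is given the untreated mean and A the treated one. It then applies a two-sample t formula with n1 + n2 − 2 degrees of freedom, where "α is the Type I error set at 0.05" and "1-β is set at 0.80". The result is 9 per intervention, 18 in total, and 26 after allowing for 30% drop-out.

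Section 2.7.1 explains that sleep indices need substitutes under sedation and makes ABI-A the primary outcome. An apnea is a complete cessation lasting more than 10 s, and "The abnormal breathing index (ABI) is calculated as the number of these abnormal breathing instances per hour of the study period".

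Section 2.6 sets the observation windows: "a baseline evaluation (i.e., no control of tongue position with TPR in place) will be performed (1 min"), then B for 1 min, and A for 1 min at MAX 50 plus 1 min at MAX 100. Section 2.8 compares baseline with A and with B. Nothing in the article gives a variance for ABI-A or converts the AHI variance to it.

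**The concern.** AHI counts apneas and hypopneas over a sleep recording. ABI-A counts apneas alone over one minute of sedation and multiplies by 60. Both are expressed per hour, but one event in a one-minute window is already 60/h, so chance variation in the count is far larger than the between-patient spread of an AHI. If the planning SD does not belong to the outcome, the sample size has no stated basis. A null result from 18 to 26 participants could then be read as evidence that tongue position does not matter, when the trial had little chance of detecting the planned difference.

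A second point concerns interpretation. The count does not rise steadily with obstruction: an airway closed for the full 60 s scores one event (60/h), while three apneas of 11 s (33 s in total) score 180/h.

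**Working it through.** **1. Reproduce the stated figure.** Inputs from section 2.5: difference 21.8 − 9.3 = 12.5/h, α 0.05, power 0.80. The article does not say which SD is σ. With σ = 8.6, d = 12.5/8.6 = 1.453. For n = 9 per group the noncentrality is 1.453 × √(9/2) = 3.08 on 16 df, and two-sided power is 82.5%; n = 8 gives 77.1%. So 9 is reproduced with SD 8.6 and a two-sided t test, and 18/0.7 = 25.7 gives 26. The choice of 8.6 is inferred from this match. The printed formula is one-directional, while section 2.8 is two-tailed; a one-sided test with SD 8.6 would need 7.

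**2. Possible values of ABI-A.** Each apnea exceeds 10 s, so one minute holds at most five. A one-minute window gives 0, 60, 120, 180, 240 or 300/h. This holds for baseline and B. It holds for A if one minute is scored (section 2.4 defines A at MAX 50). If MAX 50 and MAX 100 are pooled, A moves in steps of 30/h.

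**3. Smallest possible SD.** For a whole-number count whose mean has fractional part f, the variance is at least f(1 − f). No distribution is assumed.
- B: 21.8/60 = 0.363 events per window; SD ≥ 60 × √(0.363 × 0.637) = 28.9/h
- A, one minute: 9.3/60 = 0.155; SD ≥ 60 × √(0.155 × 0.845) = 21.7/h
- Poisson counts: 60 × √0.363 = 36.2/h and 60 × √0.155 = 23.6/h

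An SD as small as 8.6/h needs f(1 − f) ≤ (8.6/60)² = 0.0205, that is, a mean within about 1.3/h of a multiple of 60. The other printed SD (5.8) and the pooled value √((8.6² + 5.8²)/2) = 7.3 are further still below the minimum.

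**4. Power on the plan's unpaired formula.** Difference 12.5/h, 9 per group, two-sided.
- Smallest SDs: √((28.9² + 21.7²)/2) = 25.5; d = 0.489; power 16%; 67 per group needed for 80%
- Poisson: √((36.2² + 23.6²)/2) = 30.5; d = 0.409; power 13%; 95 per group needed for 80%

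**5. Power as pairs, which is what the crossover provides.** With independent Poisson counts, the SD of the difference is √(36.2² + 23.6²) = 43.2/h and d = 12.5/43.2 = 0.289, giving 21% with 18 and 29% with 26. A simulation adds between-patient variation. Individual rates are gamma with the planning means and SDs and correlation 0.5 between the two latent rates. Counts are Poisson, capped at five per minute; the test is a two-sided paired t test, with 20,000 runs per cell. The rate multiplier is an assumption, because the article gives no apnea rate under sedation.

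| Rates B / A (per hour) | 18 completers | 26 completers | 18, A pooled | 26, A pooled |
|---|---|---|---|---|
| ×1: 21.8 / 9.3 | 19% | 27% | 18% | 29% |
| ×2: 43.6 / 18.6 | 36% | 50% | 38% | 56% |
| ×4: 87.2 / 37.2 | 61% | 78% | 68% | 85% |
| ×6: 130.8 / 55.8 | 77% | 91% | 84% | 95% |

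At ×1, about 70% of B windows and 86% of one-minute A windows contain no apnea.

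**The case against.** The best counter-argument is that the sleep rate is the wrong rate. The Discussion says that upper airway muscle activity may be suppressed more under propofol than in natural sleep, and section 2.7.1 presents the sedation indices as substitutes for AHI. If apneas are several times as frequent, the difference in ABI-A grows faster than its SD and the power recovers. This stands as far as it goes: a reader might infer that ABI-A cannot reach 80% power with this sample, and the table shows that it can. But that power would rest on a rate the article never states, not on the AHI figures it cites.

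A has two minutes. Pooling them gives A steps of 30/h, so it is not established that every condition moves in steps of 60/h. Baseline and B still do, and power at the planning rates stays low.

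The study period in the ABI definition is not tied to a window. However, comparing baseline, A and B requires a separate index for each, and the whole core session averages only 6 min.

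A reader might also conclude that the primary outcome must become the percentage of time in apnea (ART-A %). The documents do not support that. It comes from the same windows, so a window without apnea still scores zero. In the same kind of simulation, with apnea durations assumed to be 10 s plus an exponential with mean 8 s and total time capped at 60 s, its power was slightly lower than that of the count: 17% against 19% with 18 completers at ×1, and 57% against 63% at ×4. The trial is non-blinded and recruitment opened on 25 April 2022, so a swap would invite questions about outcome switching. Nor does the article show how often an apnea lasts close to a full minute, so the reversal described above is possible by definition but of unknown frequency.

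**Conclusion.** The power statement is wrong as written. The minimum SD of 28.9/h at a mean of 21.8/h follows from the article's own definitions and needs no distributional assumption, so the planning SD of 8.6/h cannot describe ABI-A at that mean. At the planning rates, power is about 13–16% on the plan's formula with one-minute windows. As pairs it is about 19% with 18 completers and 27–30% with 26 (that is, with no drop-out), depending on the model and on whether A is pooled. The paired figures rest on Poisson counts; the simulated ones also assume a latent correlation of 0.5. At 4 to 6 times the planning rates, again an assumption, one-minute windows give about 61–77% with 18 and 78–91% with 26, somewhat more if A is pooled. The supportable conclusion is that 80% power has not been justified for the declared primary outcome. It does not follow that the design cannot reach it, or that the outcome must be replaced.

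**What to change.** - In section 2.5, delete the claim that 18 completers give 80% power on the AHI figures.
- Restate power, or the detectable difference, for ABI-A as measured in the actual windows and with the paired crossover comparison. State the assumed apnea rate under sedation, its source and a range, and whether A is scored at MAX 50 alone or over both minutes. Use one sidedness throughout, matching section 2.8.
- In section 2.7, state that ABI-A will be read alongside the already planned ART-A %, because the count is not monotone in obstruction. Making ART-A % primary is optional; if chosen, it needs its own power statement and a record of whether any outcome data had been seen.

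The cost is a protocol amendment with no new measurements. The stated power will probably look less favourable, and the trial may have to be presented with a larger detectable difference.
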